### Patient screening and enrollment

2.6

The blinded study assistant ([name]) recruited inpatients from the three general wards at our neurology department. First, inpatients were screened for an indication for a diagnostic LP as determined by the treating ward physicians. Inclusion and exclusion criteria were then checked, and all eligible patients were approached and informed about the option to participate and gave written informed consent for enrollment.

Patients were informed that all eligible patients undergoing lumbar punctures at our facility were currently being asked to participate in a study to evaluate the entire process and monitor the quality of care and that they would be asked to complete questionnaires at different time points before and after the LP for this purpose. We did not disclose the fact that the informed consent procedure (ICP) would be the object of the intervention and that headache as a side effect was the main outcome, as this would elicit attention to the symptom and lead to reporting bias. Instead, we stated that the study would test the implementation of a new protocol for the preparation and postprocedure management of lumbar punctures on the ward by the physician and compare this to the usual routine. Patients were told that they would be randomly assigned to one of two groups. It was emphasized that no technical aspect of the execution of the LP would be altered, irrespective of whether or not they participated in the study. In the written participant information, patients were made aware that in some studies, patients may not be fully informed about all objectives and contents of the investigation for scientific-methodological reasons, but that compliance with ethical standards is always maintained. All participants provided written informed consent before data collection.

### Sample size, randomization, and blinding

2.7

The sample size of N = 80 for the final analysis was chosen for reasons of feasibility while ensuring sufficient power to detect a clinically meaningful effect. With a power of 0.90, the study can detect an effect size f of at least 0.16 for the interaction effect between the group and time point on the primary outcome measure (headache-related impairment) (G*Power 3.1.9.7). This corresponds to a small to medium effect size. The recruitment period was set at 6 months (December 2023–May 2024), based on predetermined staff resources and estimates of the expected number of eligible study patients from recruitment from the wards. This timeline was expected to yield an effective sample size of 80 participants, accounting for an anticipated attrition rate of 15%.

Group allocation was performed after enrollment (i.e., after patients had provided written informed consent) via clustered block randomization, with a block consisting of 10 sequentially enrolled patients. To minimize the risk of communication between participants potentially influencing the outcomes, which can be a concern in settings like inpatient stays, the entire block was assigned to the same group. The sequence of all blocks was randomized before the start of the study based on a randomization list created in R. The last block of each group was truncated and ended as soon as the targeted sample size of n = 40 per group (not counting dropouts) was reached. The randomization list and the mode of randomization (clustered block randomization) were concealed from the blinded study assistant, who was responsible for recruiting and data collection, as well as from the clinical staff, to avoid unintended indirect influences from nurses or treating ward physicians. Only the study physician performing the ICP and LP according to the group allocation had the randomization list and was unblinded to group allocation.

### Protocol for standard-of-care and optimized communication

2.8

The protocols for the ICP differed between the two groups in terms of specific and predefined aspects of verbal and non-verbal communication.

First and foremost, the study physician adhered to the group-specific guiding script when orally presenting information about the indication, instructions, steps of the procedure, risks, and recommendations in the ICP. The SOC condition intended to reflect real-world clinical communication, characterized by negatively framed statements and a paucity of patient-centered interaction behaviors (Lang et al., 2005; Tackett et al., 2013; Sharp et al., 2022). Table 1 lists key elements of the group-specific guiding scripts and the communication technique in OPT. The entire guiding script for each group is provided in Supplementary Text S1. If questions from the patients arose, the physician followed predefined rules for interactions and demeanor toward the patient. The physician’s body language also differed between the two groups. In the control group, the physician stood at the patient’s bedside with arms mostly crossed, not seeking eye contact, and checking the time on their cellphone two or three times. The optimized communication protocol involved the physician sitting on a chair next to the patient, maintaining eye contact, using open gestures, and modulating their tone of voice and facial expressions to convey empathy where appropriate. Supplementary Videos S1, S2 give an impression of the informed consent procedure according to SOC and OPT in English.

**Table 1 tab1:** Key elements of the verbal information during the informed consent procedure for the standard-of-care group (SOC) and the optimized communication group (OPT).

	Standard-of-care (SOC)	Optimized communication (OPT)	*Communication strategy used*
Indication	“We need the spinal fluid to proceed with your case.”	“We’re investigating the spinal fluid to better understand how we can best help you.”	*Primacy effect, goal orientation, patient-centered narration*
	–	“We perform these spinal taps very often here. For me, it’s like drawing blood.”	*Primacy effect*
	“There is not a good alternative to investigating the spinal fluid, so unfortunately, if we want to know these results, there’s no way around it.”	“The spinal fluid is especially helpful for understanding what’s going on in the nervous system. That’s why we do it so often.”	*Positive message framing, goal orientation*
Procedural information	“You’ll sit there and arch your back. You need to tuck your chin into your chest. It’s important that you stay in this position because otherwise, it will be more difficult for me to get the needle between the spinous processes of the vertebrae into the spinal canal.”	“You’ll sit on the edge of the bed and arch your back. You can see an illustration of it here. It’s important to tuck your chin into your chest as this is the ideal position. That will already be a big help for me.”	*Positive message framing, goal orientation*
	“As you can see, here in the spinal canal, where we want to go, is also the spinal cord. We want to avoid getting close to that at all cost. That’s why I will insert the needle lower down here.”	“Here in the spinal canal there is also the spinal fluid. Sometimes patients ask me if the spinal cord is not close to that site. But I can reassure you, as that ends higher up and we are at a safe distance; our target area is down here.”	*Addressing common concerns, reassurance, positive wording*
	“The tip of the needle may touch nerve fibers, which you might feel as a brief electric shock in your leg.”	“It’s possible that we might tickle the nerve fibers during the procedure, which you might feel as a brief tingling in the leg. But when that happens, we know we are in the right spot, and we’ll already be done after a few minutes.”	*Positive wording, positive message framing*
Preamble before risk disclosure	“Unfortunately, complications cannot be completely ruled out. On this form here, various risks are listed. I will mention some of them to you.”	“As a doctor, it’s my duty to inform you about the risks of the procedure.”	*Positive wording, patient-centered narration*
	–	“However, side effects are rare, and the vast majority of patients do not notice anything afterward. You should also know that sometimes side effects occur simply because you are informed about them. Just knowing about potential side effects can alter your body’s perception; it might have happened to you before, you listen to yourself a bit more and become more aware of small changes that you would not otherwise notice. This phenomenon is called the nocebo effect, and it has been documented in many scientific studies. I can give you an example from my own experience: I was at a family gathering, and it later turned out that my nephews and nieces had headlice. You cannot imagine how much my head and everywhere else itched when I heard that, even though I did not have any lice myself in the end. So, my advice: Keep this in mind whenever you hear about side effects. It’s best to distract yourself after the procedure, perhaps by reading something.”	*Nocebo information*
Risk disclosure	“Infections, for example, are always possible when a needle is inserted into the body, as germs could potentially be introduced.”	“I will work carefully and in sterile conditions to minimize the risk of infection.”	*Stressing prevention measures*
	“Also, in principle, bleeding or tissue injury from the needle can occur, but this is very unlikely.”	“This is the most common procedure in neurology; we perform it several times a day at this university hospital, and I have never encountered a relevant bleed or injury caused by it.”	*Reassurance*
	“We will drain some spinal fluid from the body. The most common side effect that could arise from this is headache. Therefore, you might get a headache, which is worse when you are upright, so sitting or standing.”	“The body quickly replenishes the removed spinal fluid. Sometimes, patients may experience headaches, which improve significantly when lying down.”	*Positive wording*
	“Such headaches occur in about 10 percent of cases after a lumbar puncture.”	“However, the vast majority of patients, about 9 out of 10, do not experience this at all.”	*Positive attribute framing*
Recommendations	“If headaches occur, you should lie flat and drink plenty of fluids, and if necessary, you can get painkillers.”	“If you do notice any such discomfort, you can help it pass quickly by lying flat and drinking plenty of fluids. We can also support you with effective pain medication if necessary.”	*Positive wording, stressing coping mechanisms*

OPT: “I can understand if you are feeling a bit uneasy about this. I would probably feel the same way in your position. But, you know, most patients feel relieved afterward and are surprised at how well it went.” *(emotional validation, positive wording).*

The insertion of the needle tip was announced in the groups as follows:

SOC: “Caution, here comes the prick.”

OPT: “Alright, I am starting now.” *(positive wording).*

### Lumbar puncture

2.9

Lumbar puncture was performed according to the usual routine in our department. Only atraumatic systems consisting of a facet-tip introducer and an atraumatic Sprotte needle were used (PAJUNK Sprotte Lumbar). In total, 22-, 21-, or 20-gauge needles with lengths of either 90 or 120 mm were used at the physician’s discretion, based on the patient’s physique. To enable a comparison between groups, the needle size and length used, number of attempts until successful puncture of the subarachnoid space, milliliters of CSF collected, and total time spent at the patient’s bedside for LP were noted. Inpatient roommates and visitors were asked to leave the room for the duration of the procedure.

The patient was asked to sit at the edge of the bed and the bed was elevated. To ensure a stable and comfortable position, the patient’s feet rested on a chair. The patient was asked to adjust his/her position, with the chin tucked into the chest and the upper body held in a kyphotic posture. The physician disinfected her hands before any contact with the patient environment and put on non-sterile gloves and a face mask. The horizontal line between the palpable tops of the iliac crest on both sides indicates the height of the spinous process of lumbar vertebra L4. The interspinous space of lumbar vertebrae L3-L4 or L4-L5 was chosen for needle insertion. Diligent repeated, spacious disinfection of the skin (Kodan) was performed. A sterile working field with sterile swabs, adhesive bandages, and needles was prepared, and the physician disinfected her hands again and switched to sterile gloves. The insertion of the introducer was announced to the patient according to the group-specific wording. The Sprotte needle was then inserted through the introducer to enter the subarachnoid space. Upon loss of resistance (indicating penetration of the Dura), the metal stylet within the Sprotte needle was retracted to allow backflow of CSF. A target amount of approximately 10 mL of CSF was collected before inserting the stylet again and withdrawing the needle, and the patient was told that the procedure was finished, and he/she could sit up normally. A small adhesive bandage was applied at the puncture site. The patient was briefly reminded about the recommendation to rest in a supine position. The physician then left the room to take care of the processing of the CSF samples.

### Main outcome

2.10

#### Headache-related impairment

2.10.1

The main outcome is headache-related impairment, and was rated 3 h (t3), 24 h (t4), and 72 h (t5) after a lumbar puncture on a numerical rating scale (NRS) with integer values ranging from 0 (= no impairment) to 10 (maximum imaginable impairment). Patients were asked to rate their headache-related impairment since the lumbar puncture (t3) or since the last survey time point (t4, t5), respectively: “How severely have you felt impaired by headache since the lumbar puncture?” (original in German: “Wie stark fühlten Sie sich seit der Lumbalpunktion durch Kopfschmerzen beeinträchtigt?”). The construct of impairment was chosen as it allows/encourages the patient to integrate different dimensions of the individual negative pain experience (i.e., impact on activity, pain unpleasantness, pain intensity, duration) into his/her assessment.

### Secondary outcomes

2.11

Secondary outcomes are intended to provide supporting evidence for the positive effects of the intervention and explore potential modulating effects on the main outcome.

#### Expectation of unwanted effects

2.11.1

As part of an assessment of procedure-related expectations using modified items of the Treatment Expectation Questionnaire (TEX-Q) (Shedden-Mora et al., 2023), the expectation regarding the extent of unwanted side effects after LP was rated on an NRS from 0 to 10 at t2 (immediately after ICP). The precise wording of the modified questions is provided in Supplementary Text S2.

#### State anxiety

2.11.2

State anxiety was assessed immediately after ICP (t2) by calculating the total score from the 20 items of the state anxiety subscale from the State–Trait Anxiety Inventory (STAI) (Ferreira and Murray, 1983).

#### Headache incidence

2.11.3

Patients were asked if they had experienced any headache (binary yes/no response) since LP (t3) or since the last survey (t4, t5). Headache incidence describes the number of patients who experienced headache (= yes response) at any of these time points, divided by the number of all patients in the respective group.

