### Exclusion criteria

2.4

Patients were not eligible if one or more of the following criteria were met: presence of contraindications against LP, as defined in guidelines (Engelborghs et al., 2017; Tumani et al., 2019), which include elevated intracranial pressure, infection at the puncture site, use of anticoagulant medications, coagulopathy, or thrombocytopenia; emergency indication for lumbar puncture; insufficient mental capacity to provide informed consent; impaired consciousness; limited ability to complete surveys on an electronic tablet; intended therapeutic purpose of lumbar puncture (i.e., spinal tap for suspected intracranial idiopathic hypertension or normal pressure hydrocephalus); history of prior lumbar puncture (or failed attempts); extreme scoliosis, extreme obesity with BMI > 50, or other medical conditions likely to complicate lumbar puncture; indication for performing lumbar puncture under fluoroscopy; presence of a chronic headache condition according to the International Classification of Headache Disorders (ICHD)-3 criteria and/or 15 or more headache days in the last 30 days; headache as the primary complaint leading to admission or LP indication.

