#### Survey time point 1 (t1)—baseline assessments

2.12.1

After enrollment, patients completed questionnaires to assess trait anxiety and depression [trait subscale of the State–Trait Anxiety and Depression Inventory, STADI-Trait (Laux et al., 2013)] and the baseline presence and severity of the following symptoms during the past 7 days: nausea, headache, vertigo, back pain, changes of vision, hearing or sensation, and photo- or phonophobia symptoms [modified General Assessment of Side Effects, GASE (Rief et al., 2011)]. Current headache intensity was assessed on a numerical rating scale (NRS) from 0 to 10. Basic demographic and biometric characteristics were recorded (age, sex, education, height and weight, blood pressure, and heart rate at admission) as well as current medication, days with alcohol consumption per month, and nicotine consumption (in pack years). The reason for admission was stated freely (e.g., neurological symptoms or recent findings requiring further investigation). The presence of a suspected or known underlying neurological diagnosis was also recorded. Illness perception was assessed using the following three items from the Brief Illness Perception Questionnaire (modified B-IPQ) (Broadbent et al., 2006): experience of symptoms, impact on daily life, and degree of concern. Information was further obtained on patients’ prior experiences with similar procedures, that is, epidural or spinal anesthesia, and their satisfaction with these procedures. Finally, the reason for admission, indication for LP, and suspected diagnosis as given by the treating ward physicians were noted.

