#### Secondary outcomes

2.14.2

Current, mean, and maximum headache intensity will be tested using two-way repeated measures ANOVA or the non-parametric alternative, in alignment with the analysis of the main outcome. The headache incidence and the use of on-demand pain medication will be used to calculate odds ratios to compare the odds of developing headaches or using pain medication up until 72 h after LP between the OPT and SOC groups. Differences in expectations regarding the extent of unwanted side effects, state anxiety, perceived warmth and competence of the physician, and satisfaction with the procedure will be assessed using independent t-tests or Wilcoxon rank-sum tests (in the case of non-parametric data). For confirmatory analyses of group differences in the secondary outcomes, an alpha level of 0.05 after comparison for multiple testing using the Bonferroni–Holm procedure will be regarded as statistically significant.

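### Headache incidence (2.11.3) is a 72-hour period prevalence over all patients, but 2.14.2 reads its odds ratio as the odds of developing headache

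*Protocol article*

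**What the plan says.** Section 2.11.3 builds the outcome from a yes/no question about any headache since the LP (t3) or since the last survey (t4, t5). The numerator is fixed as "Headache incidence describes the number of patients who experienced headache (= yes response) at any of these time points" and the denominator as "divided by the number of all patients in the respective group".

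Section 2.14.2 says that incidence and pain medication use will yield odds ratios to "compare the odds of developing headaches or using pain medication up until 72 h after LP between the OPT and SOC groups".

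Section 2.4 limits pre-existing headache by excluding a chronic headache condition and/or "15 or more headache days in the last 30 days", and headache as the main reason for admission or for the LP.

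Section 2.12.1 records headache at t1 in two ways. The modified GASE covers "the baseline presence and severity of the following symptoms during the past 7 days: nausea, headache, vertigo, back pain" and further symptoms. In addition, "Current headache intensity was assessed on a numerical rating scale (NRS) from 0 to 10". Neither item enters 2.11.3 or the incidence analysis in 2.14.2.

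**The concern.** Incidence needs a population free of the condition at the start and a rule that the event is new. Section 2.11.3 has neither. A patient with up to 14 headache days in the past 30, or with a current headache that is not the leading complaint, may enrol. If that headache is still there after the LP, a truthful answer at t3 is yes, and the patient is an incident case, although nothing developed.

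This cannot be put down to condensation in a journal article. Numerator, denominator and interpretation are all stated, and they do not agree.

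Two effects on the odds ratio follow. A share common to both arms raises both proportions and pulls the odds ratio towards 1. A share that differs between arms moves the odds ratio without any effect on new headache. The second deserves more attention here than under individual allocation, because 2.7 assigns whole blocks of 10 consecutive patients to one group. That gives 80/10 = 8 blocks, or about 10 if 15% attrition is replaced (80/0.85 ≈ 95 patients), so there are few units to balance baseline headache.

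**Working it through.** **Plan's own figure.** There is none for this outcome. The 90% power in 2.7 concerns the group-by-time interaction on headache-related impairment and plays no part here.

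**Inputs.**
- 40 patients per group (2.1).
- Level 0.05 (2.14.2), taken as two-sided. The Holm step and the block allocation are ignored.
- *q*, the share of patients with a headache before the LP that continues after it: not in the article, assumed 0 to 30%.
- *p*, the risk of new headache in the rest: assumed 45% in the standard-of-care group (SOC) and 20% in the optimized group (OPT).

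**Formulas.** Measured proportion = *q* + (1 − *q*)·*p*. Odds ratio = odds in SOC / odds in OPT, so values above 1 favour OPT. Power is the normal approximation for two proportions, with 40 per arm for the present definition and 40·(1 − *q*) per arm when restricted to patients headache-free beforehand.

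**Equal share in both arms.** At *q* = 10%: SOC 0.10 + 0.90 × 0.45 = 0.505; OPT 0.10 + 0.90 × 0.20 = 0.280; odds ratio (0.505/0.495)/(0.280/0.720) = 1.020/0.389 = 2.6.

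| *q* | SOC measured | OPT measured | Odds ratio | Power, all 40 per arm | n per arm restricted | Power restricted |
|---|---|---|---|---|---|---|
| 0% | 45.0% | 20.0% | 3.3 | 67.1% | 40 | 67.1% |
| 5% | 47.8% | 24.0% | 2.9 | 60.4% | 38 | 64.8% |
| 10% | 50.5% | 28.0% | 2.6 | 54.1% | 36 | 62.4% |
| 20% | 56.0% | 36.0% | 2.3 | 43.3% | 32 | 57.2% |
| 30% | 61.5% | 44.0% | 2.0 | 34.5% | 28 | 51.5% |

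Restriction leaves the odds ratio at 3.3 in every row. Under these assumptions it loses less power than the dilution does, despite the smaller groups.

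**Unequal share, no effect on new headache.** Take *p* = 30% in both arms and *q* = 25% in SOC against 10% in OPT. Measured: 0.25 + 0.75 × 0.30 = 47.5% and 0.10 + 0.90 × 0.30 = 37.0%; odds ratio (0.475/0.525)/(0.370/0.630) = 1.5. With the shares exchanged it is 0.65. In whole patients this is about 19/40 against 15/40, for which Fisher's exact test gives p ≈ 0.50.

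**The case against.** The strongest reply is that the randomised contrast is sound as it stands. Any headache within 72 hours, over everyone in the group, is explicit and reproducible, and a nocebo trial has good reason to count every headache a patient reports. Pre-existing headache shared by both arms only dilutes. This stands: the defect lies in the name and the interpretation, and no invalid comparison follows from it.

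The second reply concerns size. The exclusions in 2.4 remove the patients most likely to bring a persisting headache, the remaining share is not given, and the table assumes that every such patient answers yes. At 5% the power loss is about seven points (67.1% to 60.4%), and restriction recovers about four. The imbalance example moves the estimate but is far from significance. The outcome is secondary, and 2.11 describes such outcomes as supporting evidence. All of this stands and limits the weight of the point.

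A reader might also infer that the result could not be set beside the earlier small study (47% against 8%) or the roughly 10% figure for headache after LP. The article does not support either inference. The Introduction describes the earlier study as a count of reported headache over all patients per group and says nothing of how prior headache was handled. Postdural puncture headache is a specific diagnosis, which any headache would not match even with baseline headache removed; the features needed to classify it are collected separately (2.12.5).

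It may also be tempting to class patients with headache at t1 as worsened when their later maximum exceeds the t1 score. That sets a maximum over up to 72 hours against one momentary rating, so ordinary fluctuation would count as worsening in both arms.

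**Conclusion.** The point holds as a mismatch between definition and interpretation. Section 2.11.3 defines a 72-hour period prevalence, and 2.14.2 reads it as the odds of developing headache. With an equal share of persisting pre-LP headache, the odds ratio understates the effect on new headache; with an unequal share, it can move in either direction.

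The size cannot be determined from the article. Under the assumed risks of 45% and 20%, a share of 5% to 30% turns an odds ratio of 3.3 into 2.9 to 2.0. Those risks, the shares and the certain persistence are all assumptions. The definition of the primary outcome is not affected by this point.

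**What to change.** 1. In 2.11.3, rename the present all-patient measure, for example to *any headache within 72 h*, and reword 2.14.2 so that its odds ratio compares the odds of having any headache in that period.
2. Before the groups are compared, add one of two analyses: an incidence analysis limited to patients with current headache intensity of 0 at t1, or an odds ratio for the all-patient measure adjusted for t1 headache. For the incidence analysis, use absence of headache on the 7-day modified GASE item as a stricter sensitivity definition.
3. Report the share of patients with headache at t1 by group, so that readers can judge dilution and imbalance.

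No new data are needed. Recruitment is over, but section 2.14 describes the analysis as still to come, so the change should be dated and documented; if the groups have already been compared, it should be labelled post hoc. The restricted analysis has a smaller denominator (36 per arm at a 10% share). The t1 rating is momentary and precedes the consent discussion and the LP, so a headache starting between t1 and the LP still counts as new; this should be stated as a limitation.
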